#### Data monitoring and management

Based on previous evaluations of body image interventions among young people [40, 41], this intervention and trial protocol are deemed low risk for participant safety and therefore an independent data monitoring committee was not established. However, the research team will monitor survey responses for data quality, including completeness, consistency, and plausibility. All survey data, including informed consent and self-report measures, will be downloaded from a university approved survey software (Qualtrics), and securely stored in a password protected data file on a university approved cloud storage (i.e., OneDrive). At the start of each survey (e.g., T1, T2, T3, T4), participants will create a unique identification code, which will allow responses to be matched across time points. Personal data (i.e., name, geographical location, email address) of coaches, parents, and girls will be stored separately to survey data (i.e., outcome measures), with both datafiles securely stored in a password protected datafile on the university cloud storage. Personal data will be deleted once the trial is complete. Audio recordings will be used to assess intervention fidelity and will be securely stored on the university cloud server. Once the fidelity inter-rater reliability assessments are complete, these recordings will be permanently deleted. Anonymised survey data will be made available on reasonable request for non-commercial purposes.

#### Statistical power

A meta-analysis of 31 studies evaluating interventions that target the intersection of body image and movement experiences among girls and women via randomised controlled trials reported a mean effect size of Cohen’s *d* = 0.18 on body image, which can be interpreted as a small-to-medium effect size. Based on conservative *d* = 0.2, an ICC of 0.02 within intervention delivery groups (as informed by a similar cluster trial of a body image intervention Craddock, Budhraja, Garbett, Nasution, Gentili, Rizkiah, Saraswati, Medise, White, Diedrichs & Williamson: Randomised Control Trial of Dove Confident Me Indonesia: Single Session. Forthcoming]), and an approximate distribution of 15 athletes per delivery group, a total sample size of 864 athletes (*N* = 432 per arm) would provide 90% power over a correlation between baseline and outcome data at T2 or about 0.6, considering alpha = 0.05. We will oversample to mitigate the effects of loss at post-intervention due to athletes’ absence or any other logistical difficulty. Therefore, the ideal sample size will be increased by 20%, leading to a minimum target of approximately 1,036 athletes (518 per randomised arm).

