**Methods:**

Following co-creation and an initial pilot, a two-armed cluster randomised controlled trial will assess the immediate (post-intervention) and short-term (1-month and 3-month follow-up) impact of BCA on girls’ (*N* = 1,036; 11–17 years old) body image, sports enjoyment, and affect. Sport organisations will be randomly allocated (1:1) into either an intervention or waitlist control condition. Girls and coaches in the intervention condition will complete three 60-minute sessions over three consecutive weeks. The primary outcome will be the immediate change in girls’ body esteem, with secondary outcomes assessing the immediate and short-term changes in girls’ body appreciation, self-objectification, attuned self-care, sports enjoyment, and affect.

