#### Pilot findings

Initially, eight organisations were recruited for participation in the pilot trial, with four organisations dropping out at baseline (i.e., due to staff turnover or scheduling clashes). Girls and coaches from four organisations saw the pilot to completion, including completing baseline and post-intervention assessments, and completing five 60-minute sessions over five consecutive weeks (see supplementary Fig. 1 for design and participant flow). A total of 26 girls participated in the pilot (*M*_*age*_ = 12.73 [*SD* = 1.99];* n* = 13 in intervention; *n* = 13 in control). Nineteen girls completed baseline assessments (*n* = 10 in intervention; *n* = 9 in control), with 12 providing post-intervention data (*n* = 7 in intervention; *n* = 5 in control). A majority of girls identified as White (34.61%, *n* = 9), followed by 23.07% (*n* = 6) as Hispanic, 19.23% (*n* = 5) as Black, 11.54% (*n* = 3) as Asian, 7.69% (*n* = 2) as multi-racial, and one preferred not to say. Participants had been a member of their sport organisation for an average of 3.38 years (*SD* = 1.52). Girls in the two arms did not significantly differ on any of the demographic variables. A total of seven female coaches (*M*_*age*_ = 29.71 [0.92]; *n* = 4 in intervention; *n* = 3 in control) participated in the pilot. All coaches completed baseline assessments; however, only three coaches from the intervention condition provided post-intervention data. Three coaches were Black (42.85%), three were White (42.85%), and one was multi-racial (14.28%). Coaches had been a member of their sport organisation for an average of 3.00 years (*SD* = 1.40). Coaches in the two arms did not significantly differ on any of the demographic variables.

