Following the onboarding process, organisations will be randomised into either the intervention (Block A) or waitlist control (Block B) condition (see Fig. 1 for participant flow). Those assigned to Block A will be advised to schedule the intervention between the 6^th^ February and 2^nd^ April 2023, while those assigned to Block B will be advised to schedule their delivery after the 2^nd^ July 2023. Three weeks prior to intervention delivery, coaches and parents will complete informed consent via an online survey. Following parental consent, girls in both conditions will complete informed assent and baseline assessments of primary and secondary outcomes via an online survey one week prior to intervention delivery. Girls will be encouraged to complete the surveys in the privacy of their homes; however, coaches agreed to make surveys accessible immediately before session one (e.g., girls will attend 20 min early and complete via a mobile device), should girls have difficulty completing the survey on their own accord. The intervention will be delivered in the team’s usual practice space, with logistics regarding equipment and space accessibility coordinated and confirmed with coaches during the onboarding call with the research team. At the end of the intervention period (i.e., 3 weeks), both conditions will be assessed on primary and secondary outcomes, and again at 1-month and 3-month follow-up. Following the final assessment, the waitlist control group will complete the intervention; however, their engagement will not be monitored or assessed. Lastly, to compensate participants for their time, they will receive an electronic voucher, with girls receiving US$60, coaches receiving $100, and organisations receiving $200.

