#### Randomisation and blinding

Randomisation will occur at the group level (1:1). The randomisation sequence will be generated using a computer software, with clusters randomised into the intervention or control condition. Randomisation will be conducted by an experienced researcher who is external to the authoring research team and the conditions will be masked. Throughout the recruitment and onboarding processes, group allocation will be masked to participants. The intervention group will be referred to as Block A and the control condition referred to as Block B. Coaches and/or organisations delivering the intervention will be advised that two scheduling blocks have been created due to the magnitude of participants. Study hypotheses will also be masked from participants. Lastly, data analysts will be unaware of condition allocation (dummy coded) when conducting statistical analyses on primary and secondary outcomes.

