#### Data analyses

Data preparation, assessment of baseline equivalence, hypothesis testing, and exploration will be undertaken using SPSS 28.0 (IBM Corp, 2021) and R Studio (R Core Team, 2021). Data will be screened to ensure scoring fidelity and data accuracy. Once the data validity checks are complete, scales’ scores will be calculated, score distributions will be assessed, and the data will be checked for outliers and any inaccurate influential observations. Missing data will be assessed across all outcomes and time points. Data will be analysed on an intention-to-treat basis and secondly using data from participants with at least 70% of the attention checks successful completed.

The primary analyses will be linear mixed models with random intercepts for all outcome measures (body esteem, body appreciation, self-objectification, attuned self-care, sports enjoyment, and affect). The models will include two main effects: study phase (i.e., repeated measures fixed effect factor with three levels: T2, T3, and T4), randomised arm (i.e., between-subjects fixed effect factor with two levels: intervention and control), as well as baseline levels of the outcome as a covariate. The model will also see two two-way interactions (i.e., randomised arm by study phase, randomised arm by baseline). Analyses will be run on an intention-to-treat basis, both with and without clusters including a random effect (i.e., intervention delivery group), in order to identify their potential significant impact [54].

For each outcome measure, a priori ANCOVAs will compare the two randomised arms at T2, controlling for baseline measures as covariates. These analyses will be repeated at T3 and T4. If the homogeneity of regression lines assumption is violated, the ANCOVA model will include a baseline by randomised arm interaction. Exploratory moderation and mediation analyses will be run to check whether any differences in intervention efficacy might be dependent on relevant demographic or baseline variables. To ensure valid statistical inferences, we will check for any potential assumption violation in all the models.

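### Organisations are named as the randomised unit, but the sample size and the only cluster random effect are set at the delivery group, and nothing says the two units coincide

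*Protocol article*

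**What the plan says.** The randomised unit is described in three places in the Protocol article:

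- Abstract, Methods: "Sport organisations will be randomly allocated (1:1) into either an intervention or waitlist control condition".
- Participant recruitment and procedure: "organisations will be randomised into either the intervention (Block A) or waitlist control (Block B) condition".
- Randomisation and blinding: "Randomisation will occur at the group level (1:1"). This section also refers to clusters, but does not say whether the group is the organisation or the delivery group.

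The clustering is then set at a different unit:

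- Statistical power fixes both the ICC and the cluster size at the delivery group: "d* = 0.2, an ICC of 0.02 within intervention delivery groups" and "an approximate distribution of 15 athletes per delivery group, a total sample size of 864 athletes".
- Data analyses fits the mixed models with and without "clusters including a random effect (i.e., intervention delivery group"). No organisation term is named, and the ANCOVAs at T2, T3 and T4 are described with no cluster term.

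The article gives no number of organisations, no number of delivery groups per organisation and no organisation-level ICC. It does not say that an organisation contributes only one group.

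**The concern.** In a cluster trial, the information about the arm contrast comes from the units that were independently allocated. If an organisation with two teams is allocated once, its two teams are not two independent draws. They share the allocation, and may share facilities, staff culture and peers. A model whose highest level is the delivery group treats them as independently randomised. Any positive correlation between girls in different groups of the same organisation then goes uncounted. The standard error of the arm effect is too small, the degrees of freedom are counted from groups rather than organisations, and the test rejects too often under the null. The power figure is optimistic for the same reason.

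This bears on the validity of the primary p-value. Recruiting more girls does not cure an analysis set at the wrong level.

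**Working it through.** **Inputs from Statistical power:** d = 0.2; ICC 0.02 within delivery group; 15 girls per group; baseline–outcome correlation about 0.6; alpha 0.05 (sidedness not stated, but two-sided reproduces the figure); 90% power; 864 girls, 432 per arm.

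**Assumed, because the article does not give them:** k, the number of delivery groups of 15 per organisation; and ρ, the correlation between girls in different groups of the same organisation. The within-group ICC of 0.02 already contains any organisation component, so 0.02 is the upper limit for ρ. At that limit, teammates are no more alike than girls on different teams of one organisation.

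**Step 1: reproduce 864.**

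- Unadjusted, per arm: 2 × ((1.960 + 1.282) / 0.2)² = 525.4.
- Baseline adjustment: × (1 − 0.6²) = × 0.64, giving 336.2.
- Design effect at the delivery group: 1 + (15 − 1) × 0.02 = 1.28, giving 430.4, that is 431 per arm and 862 in total, against 864 stated.
- Power at 432 per arm: Φ(0.2 / √(2 × 0.64 × 1.28 / 432) − 1.96) = Φ(3.248 − 1.96) = 90.1%.

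The arithmetic is sound. It works with the design effect taken at the delivery group.

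**Step 2: move the design effect to the organisation.**

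- DE = 1 + 14 × 0.02 + 15 × (k − 1) × ρ.
- Power = Φ(0.2 / √(2 × 0.64 × DE / 432) − 1.96).
- Type I error when only the delivery group is modelled = 2 × (1 − Φ(1.96 × √(1.28 / DE))).

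Example, k = 2 and ρ = 0.02: DE = 1.28 + 15 × 0.02 = 1.58. Power = Φ(2.923 − 1.96) = 83.2%. Type I error = 2 × (1 − Φ(1.764)) = 7.8%.

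| k | ρ | DE | Power at 864 | Total for 90% power, before the 20% uplift | Type I error, delivery-group effect only |
|---|---|---|---|---|---|
| 1 | any | 1.28 | 90.1% | 862 | 5.0% |
| any | 0 | 1.28 | 90.1% | 862 | 5.0% |
| 2 | 0.005 | 1.355 | 88.4% | 912 | 5.7% |
| 2 | 0.01 | 1.43 | 86.7% | 962 | 6.4% |
| 2 | 0.02 | 1.58 | 83.2% | 1,064 | 7.8% |
| 3 | 0.005 | 1.43 | 86.7% | 962 | 6.4% |
| 3 | 0.01 | 1.58 | 83.2% | 1,064 | 7.8% |
| 3 | 0.02 | 1.88 | 76.4% | 1,266 | 10.6% |

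**Step 3: degrees of freedom.** 864 / 15 = 57.6 delivery groups, or about 56 degrees of freedom for the arm contrast. With two groups per organisation there are 57.6 / 2 = 28.8 organisations (about 27 degrees of freedom), and with three 57.6 / 3 = 19.2 (about 17). The table uses normal approximations throughout. A t reference lowers every power figure a little, including the starting one, which becomes 89.1% on about 56 degrees of freedom.

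**The case against.** The best defence is that the units may be the same. Randomisation and blinding says group level and clusters, Data analyses explains clusters as delivery groups, and recruitment is addressed to coaches and/or organisations. That would fit one coach-led group per enrolled unit. This cannot be ruled out, and if it is so the power figure and the delivery-group model stand. But the article does not say it, and the abstract and procedure both name organisations. The wording would still need reconciling.

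It may also be said that nested random effects and degrees-of-freedom methods belong in a statistical analysis plan that is not shown. That is fair for the fine detail. It does not cover the level of clustering, which this article itself fixes in two sections.

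Three stronger readings are tempting and should not be made:

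- **That the pilot shows several groups per organisation.** Pilot findings reports that "Girls and coaches from four organisations saw the pilot to completion" and "A total of seven female coaches" took part. Coaches are not delivery groups, since several may deliver one group together. The pilot had 26 girls in all, which over four organisations is 6.5 each, under half of one planned group of 15. The text does not clearly tie all seven coaches to those four organisations either. No groups-per-organisation figure can be taken from it.
- **That the stated power and error rate hold only with one group per organisation.** They also hold if groups in one organisation are no more alike than groups in different ones.
- **That the worst rows of the table are the expected ones.** They use the limiting correlation of 0.02. With two groups and 0.005 to 0.01 the loss is modest.

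The 20% oversampling does not answer the point, because Statistical power assigns it to loss at post-intervention.

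**Conclusion.** The concern holds as a mismatch between the stated randomised unit and the unit used for both power and analysis. Harm is conditional on two things the article leaves open: more than one delivery group in at least some organisations, and positive correlation between those groups. Under the assumed values, the effect runs from slight (two groups, ρ = 0.005) to material (three groups, ρ = 0.02). A reader might infer that the planned model is certainly wrong, or that clustering is wholly disregarded. The article supports neither: clustering is allowed for at the delivery group, and that is sufficient if the units coincide. What it does support is that the validity of the primary test depends on a fact that is not stated, and that this should be settled before any unblinded analysis.

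**What to change.** 1. Name one randomised unit in the abstract, the procedure, the randomisation section, the power calculation and the analysis.
2. If every organisation supplies exactly one delivery group, say so. That sentence resolves the point.
3. Otherwise, include a random intercept for the organisation in every primary mixed model and every ANCOVA, with delivery group nested within it where an organisation has several, and base degrees of freedom on the number of randomised organisations.
4. Restate power with the design effect at the organisation level, for example at 15, 30 and 45 girls per organisation, with the assumed between-group correlation shown.

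The cost is wording and a restated, possibly less favourable, power figure. The analysis change needs no extra participants. One practical check is needed: Table 4 does not list organisation among the recorded variables, and surveys are matched by a self-created code with personal data held separately. The sponsor should confirm that organisation and delivery group can both be attached to each survey record.

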#### Data analyses

Data preparation, assessment of baseline equivalence, hypothesis testing, and exploration will be undertaken using SPSS 28.0 (IBM Corp, 2021) and R Studio (R Core Team, 2021). Data will be screened to ensure scoring fidelity and data accuracy. Once the data validity checks are complete, scales’ scores will be calculated, score distributions will be assessed, and the data will be checked for outliers and any inaccurate influential observations. Missing data will be assessed across all outcomes and time points. Data will be analysed on an intention-to-treat basis and secondly using data from participants with at least 70% of the attention checks successful completed.

The primary analyses will be linear mixed models with random intercepts for all outcome measures (body esteem, body appreciation, self-objectification, attuned self-care, sports enjoyment, and affect). The models will include two main effects: study phase (i.e., repeated measures fixed effect factor with three levels: T2, T3, and T4), randomised arm (i.e., between-subjects fixed effect factor with two levels: intervention and control), as well as baseline levels of the outcome as a covariate. The model will also see two two-way interactions (i.e., randomised arm by study phase, randomised arm by baseline). Analyses will be run on an intention-to-treat basis, both with and without clusters including a random effect (i.e., intervention delivery group), in order to identify their potential significant impact [54].

For each outcome measure, a priori ANCOVAs will compare the two randomised arms at T2, controlling for baseline measures as covariates. These analyses will be repeated at T3 and T4. If the homogeneity of regression lines assumption is violated, the ANCOVA model will include a baseline by randomised arm interaction. Exploratory moderation and mediation analyses will be run to check whether any differences in intervention efficacy might be dependent on relevant demographic or baseline variables. To ensure valid statistical inferences, we will check for any potential assumption violation in all the models.

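### The primary random-intercept model over T2–T4 implies one residual variance and one baseline slope per arm at every visit, so visit-specific standard errors are off if the baseline-adjusted variance changes with time

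*Protocol article*

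**What the plan says.** In the protocol article, Data analyses, the analysis labelled primary is set out as "The primary analyses will be linear mixed models with random intercepts for all outcome measures". Study phase is a three-level repeated factor (T2, T3, T4), arm is a two-level factor, and the baseline score is a single covariate. The interactions are then listed: "The model will also see two two-way interactions (i.e., randomised arm by study phase, randomised arm by baseline"). Baseline by phase is not among them. No residual covariance structure is named. The model is to be run with and without a random effect for the delivery group.

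The same section plans separate ANCOVAs at T2, T3 and T4, each adjusted for baseline, and promises a check of assumptions in all models.

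Table 2 places T2, T3 and T4 at days 22, 50 and 106 from baseline. The Abstract makes the immediate change in body esteem the primary outcome, so T2 is the key contrast. The Background hypothesises benefit at 1 and 3 months as well. The Statistical power section relies on "a correlation between baseline and outcome data at T2 or about 0.6" and gives no correlation for T3 or T4.

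**The concern.** A random-intercept model with no further residual structure normally means equal variance at every visit and equal correlation between any two visits. Without a baseline-by-phase term, each arm also has one baseline slope for all three visits. These are strong constraints for visits that span 84 days (day 22 to day 106).

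The precision of a baseline-adjusted contrast depends on how much variance baseline explains at that visit. If baseline predicts T2 better than T4, the adjusted variance is smaller at T2 and larger at T4. The model replaces both by an average. The T2 test then loses some power, and the 3-month interval is too narrow. If the adjusted variance falls over time, both errors change sign. Either way the visit-specific standard errors depend on an assumption that the trial does not need to make.

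**Working it through.** **Inputs from the article (Statistical power).** "Based on conservative *d* = 0.2, an ICC of 0.02 within intervention delivery groups"; "an approximate distribution of 15 athletes per delivery group"; baseline correlation 0.6 at T2; "considering alpha = 0.05" (taken as two-sided); 432 girls per arm; 90% power.

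**The plan's own figure.** Design effect = 1 + 14 × 0.02 = 1.28. Per arm, n = 2 × ((1.960 + 1.282)/0.2)² × (1 − 0.6²) × 1.28 = 430.4, so 431 per arm against 432 stated. At 432 per arm, SE = √(2 × 0.64 × 1.28/432) = 0.0616 and power is 90.1%. The stated sample size is reproduced.

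**Assumptions, not in the article.** Outcome SD equal to 1 at every visit, complete data, and a set of baseline correlations r at T2/T3/T4.

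**Formula.** With one common slope, the actual adjusted variance at visit t is 1 − r_t² + (r_t − mean r)². The model uses the average of the three at every visit. The ratio of model SE to actual SE is √(average/actual). T4 two-sided error is 2 × (1 − Φ(1.96 × ratio)). T2 power is Φ((0.2 − 1.96 × model SE)/actual SE).

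**Worked case, 0.6/0.5/0.4 (mean 0.5).**
- Actual variances: 0.64 + 0.01 = 0.65; 0.75; 0.84 + 0.01 = 0.85. Average 0.75.
- SE ratios: T2 √(0.75/0.65) = 1.074; T4 √(0.75/0.85) = 0.939.
- Model SE = √(2 × 0.75 × 1.28/432) = 0.0667. Actual T2 SE = √(2 × 0.65 × 1.28/432) = 0.0621.
- T2 power = Φ((0.2 − 0.1307)/0.0621) = 86.8%. T4 error = 6.6%.

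**Range.**

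| r at T2/T3/T4 | T2 ratio | T2 power | T4 ratio | T4 error |
|---|---|---|---|---|
| 0.6/0.6/0.6 | 1.000 | 90.1% | 1.000 | 5.0% |
| 0.6/0.55/0.5 | 1.042 | 88.5% | 0.963 | 5.9% |
| 0.6/0.5/0.4 | 1.074 | 86.8% | 0.939 | 6.6% |
| 0.6/0.45/0.3 | 1.097 | 85.1% | 0.925 | 7.0% |

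**Which constraint matters.** In the worked case the shared slope moves the T2 variance only from 0.64 to 0.65, an SE change of √(0.65/0.64) − 1 = 0.8%. The single between-visit correlation does not affect the T2 or T4 SE with complete data. Nearly all of the error comes from the common residual variance.

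**Sensitivity to the SD.** Keep 0.6/0.5/0.4 but let the SD run 1, 0.93, 0.87. The adjusted variances become 0.657, 0.649 and 0.651, and the effect disappears. With SD 1, 0.9, 0.8 it reverses: T2 ratio 0.959, T4 ratio 1.046.

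**Simulation.** 6,000 trials per scenario, 29 groups of 15 per arm, between-visit correlations 0.7/0.6/0.7. Without clustering, 0.6/0.5/0.4 gives ratios of 1.08 (T2) and 0.94 (T4), with T4 error 6.2%, in line with the formula. With ICC 0.02 and a group intercept, the same fade gives 1.03 and 0.91, with T4 error 7.8%. In that clustered setting the ratios are already 0.97 and 0.96 with no fade, so part of the T4 shortfall is not due to fading, and the T2 excess starts from a lower point.

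**The case against.** The strongest reply has four parts.

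- **The common variance is not written down.** This is correct. A reader might infer that the article expressly fixes equal variances and correlations, but it names no residual structure, and a random intercept does not by itself exclude phase-specific variances. The common variance is the usual reading, not a stated rule. The missing baseline-by-phase term is explicit, but it contributes under 1%. What remains is that the random part is described, the interactions are listed, and the ordinary implementation of that description carries the constraint.
- **The per-visit ANCOVAs avoid all three constraints.** This is also correct, and the sample-size formula has the form of a T2 ANCOVA. A reader might infer that the trial is therefore under-sized; it is not shown to be, since 432 per arm reproduces. But the mixed model is the analysis called primary. No cluster term is stated for the ANCOVAs, and without one the simulated type I error is about 8% at ICC 0.02.
- **Fading is assumed.** The article gives no T3 or T4 correlation, and Table 2 labels the primary outcome a trait measure. The size therefore stays conditional, also on a roughly constant SD.
- **Assumptions will be checked.** The promise is general, and no alternative is named for the mixed model if the check fails.

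A reader might also infer that dropout would turn the misspecified covariance into biased estimates. That is possible in principle, but the article gives nothing from which to size it, and it is not claimed here.

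**Conclusion.** The point holds in a modest, conditional form. Read in the usual way, the primary model pools the residual variance across three visits for which the article gives no reason to expect equality. If the adjusted variance differs by visit, the visit-specific standard errors are wrong, in a direction set by whether it rises or falls.

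The tabulated losses need both a fading baseline correlation and a roughly stable SD, and neither is documented. Under a rising variance the T2 error is conservative: it costs power and does not create false positives on the primary outcome. The anti-conservative error falls on the 3-month contrast, which is secondary. The change is worth making because it removes the dependence on these assumptions at little cost, not because a large error has been demonstrated.

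**What to change.** In the primary model, prespecify:

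- an unstructured within-girl residual covariance over T2–T4, or at least phase-specific residual variances, which give most of the gain; the unstructured form takes the place of the girl-level intercept;
- a baseline-by-phase term;
- the delivery-group random effect, retained;
- the random-intercept form as the named fallback if the model does not converge.

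The cost is a change of wording and code. The unstructured form has six covariance parameters in place of two, and baseline by phase adds two more, so there are about six extra parameters against a target of 1,036 girls. There is a small convergence risk, which the fallback covers.

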#### Measures

Research measures are presented in Table 4. One measure was purpose-built for the current research (i.e., girls’ comprehension of the intervention content). The remaining measures have been validated and widely used among adolescent girls, particularly in the US.

**Table 4 Tab4:** Research outcomes and internal consistencies

Demographics	Age, gender identity, ethnicity, race, disability, state and region of residence, years playing sport	T1
Primary outcome		
Body Esteem	Body Esteem Scale for Adolescents & Adults (BESAA) [38] Appearance Esteem (AE; 10 items; e.g., I like how I look in photos) and Weight Esteem (WE; 8 items; e.g., I am satisfied with my weight) subscales Mean subscale scores range between 0 (never) and 4 (always). Higher scores reflect higher esteem The BESAA has shown good internal consistency reliability (Cronbach’s α = 0.76–0.96) and evidence of validity (correlations with self-esteem) in prior research conducted with adolescents [38, 43] The BESAA has been shown to detect change in body esteem at post-intervention [40, 44] and 1–6-month follow-up [40, 41, 45, 46] in interventions targeting adolescent girls	T1–T4
Secondary outcomes		
Body Appreciation	Body Appreciation Scale – 2 (BAS–2) [37] 10 items related to body appreciation (e.g., I take a positive attitude towards my body) Mean subscale scores range between 1 (never) and 5 (always). Higher scores reflect higher body appreciation The BAS–2 has shown good internal consistency reliability (Cronbach’s α = 0.86–0.93) and evidence of validity (correlations with self-esteem, body pride, life satisfaction) in prior research conducted with adolescents [46, 47] The BAS–2 has been shown to detect change in body appreciation at post-intervention [48] in interventions targeting adolescent girls	T1–T4

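### The arm-by-baseline interaction follows three different rules in the analysis section, and the baseline score at which the arm effect is read is never stated

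*Protocol article*

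**What the plan says.** All of this is in the protocol article, mainly under Data analyses.

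- **Mixed model.** Linear mixed models are named as the primary analyses for every outcome. They contain phase (T2, T3, T4) and arm, described as main effects, the baseline score as a covariate, and "two two-way interactions (i.e., randomised arm by study phase, randomised arm by baseline". Neither interaction is conditional.
- **ANCOVA.** Arms are also compared at T2, and again at T3 and T4, adjusting for baseline. Here the interaction is conditional: "If the homogeneity of regression lines assumption is violated, the ANCOVA model will include a baseline by randomised arm interaction".
- **Moderation.** The same paragraph classes as exploratory the analyses of whether efficacy depends on demographic or baseline variables.
- **Scale.** For the primary outcome, Table 4 states "Mean subscale scores range between 0 (never) and 4 (always". All the secondary outcome scales in Table 4 run from 1 to 5.
- **Power.** Statistical power assumes d = 0.2, "an ICC of 0.02 within intervention delivery groups" and "an approximate distribution of 15 athletes per delivery group", and concludes that "a total sample size of 864 athletes (*N* = 432 per arm) would provide 90% power". The baseline correlation it uses is with the T2 outcome. No interaction enters that calculation.

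The article does not say whether baseline is centred, or which contrast from the mixed model is the treatment effect.

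**The concern.** Once arm-by-baseline is in a model, there is no single arm effect. The effect is a straight line in the baseline score, and the arm coefficient is the height of that line where the baseline variable equals zero. If baseline is centred, zero is the average girl. If it is left on its raw scale, zero is a girl at the very bottom of the body esteem scale, and on the secondary scales it is a score nobody can have. The two readings estimate different quantities with very different precision.

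The article fixes the term in one model, makes it depend on the data in another, and calls the same kind of moderation exploratory in a third place. An analyst following the text could therefore report different treatment effects for the same T2 comparison. In the ANCOVA, a preliminary check would decide which one is reported. At stake is whether the headline estimate is the average effect for which the trial was sized.

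**Working it through.** **1. Reproduce the plan's own figure.** Inputs from Statistical power: d = 0.2, ICC 0.02, 15 per delivery group, baseline correlation 0.6, alpha 0.05 (taken as two-sided), power 90%.

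- Design effect: 1 + 14 × 0.02 = 1.28.
- Variance left after baseline adjustment: 1 − 0.6² = 0.64.
- n per arm = 2 × [(1.96 + 1.2816)/0.2]² × 0.64 × 1.28 = 525.4 × 0.64 × 1.28 = 430.4, so 431.

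The article states 432 per arm, so its figure reproduces. At 432 per arm, SE = √(0.64 × 1.28 × 2/432) = 0.0616 and 0.2/0.0616 = 3.25, which gives power of 90.1%. A one-sided test would need 351 per arm and does not match. The stated 90% therefore belongs to a baseline-adjusted T2 difference with no interaction.

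**2. Arm effect with the interaction, read at the mean baseline.** The standard error is essentially unchanged, so power is 90.1% by formula. The interaction itself costs nothing here.

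**3. Arm effect with the interaction, read at baseline 0.** The variance is multiplied by 1 + (mean/SD)², where mean and SD are those of the baseline score. Power = Φ(3.25/√(1 + (mean/SD)²) − 1.96) plus the small opposite tail. The article gives no baseline mean or SD, so the ratio is an assumption and is shown as a range:

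| Assumed mean/SD | SE multiplier | Power | Power, between-cluster part of the variance not inflated |
|---|---|---|---|
| 1 | 1.41 | 63% | 69% |
| 2 | 2.24 | 31% | 36% |
| 3 | 3.16 | 18% | 21% |
| 4 | 4.12 | 12% | 15% |

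The last column is the more favourable variant, in which clustering does not add to the inflation.

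**4. Simulation check.** 2,000 trials were simulated with 29 clusters of 15 per arm, a uniform effect of 0.2 SD, and an assumed baseline mean of 2.2 and SD of 0.8 (ratio 2.75). The rejection rates were:

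- raw-scale arm coefficient: 21.5% (formula 19.9%, or 23.8% for the favourable variant);
- centred interaction: 88.5%;
- no interaction: 88.5%.

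**5. The conditional rule in the ANCOVA.** Take the same assumed ratio of 2.75, a uniform true benefit of 0.2, and a slopes check run as a 5% test. The check then fires by chance in about 5% of trials. The within-cluster SE of the interaction slope, per baseline SD, is √(0.64 × 0.98 × 2/432) = 0.054, so a slope that just reaches significance is 1.96 × 0.054 = 0.106. Carried from the mean down to 0, it shifts the arm effect by 2.75 × 0.106 = 0.29, which is more than the true benefit of 0.2. A chance slope in the positive direction therefore usually turns the raw-scale arm coefficient negative. Simulation agrees: the sign was wrong in about half of the trials where the check fired. This also disappears if the effect is read at the mean baseline.

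**The case against.** The strongest reply is that the article does not say baseline is entered raw, nor that the arm coefficient is the test. Listing arm as a main effect describes a model term, not an estimand. Coding of covariates and choice of contrast are details that a condensed article may leave to an analysis plan, which is not at hand. The model also contains arm by phase, so under reference coding a lone arm coefficient would refer to one phase in any case, and some explicit contrast must be intended. Finally, the stated power refers to a T2 comparison, and the prespecified T2 ANCOVA has no interaction by default.

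Most of this stands. A reader might infer that the primary analysis has about 20% power instead of 90%. The documents do not support that. It requires a decision against centring that nobody has written down, a baseline mean and SD that the article does not give, and disregard of the default T2 ANCOVA, which keeps about 90%.

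The reply does not remove the conflict in what is written. The same term is compulsory in the models called primary and data-dependent in the ANCOVA, while moderation by baseline is called exploratory. Those are stated rules, not omissions, and they make the evaluation point matter.

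**Conclusion.** The concern holds as an inconsistency in a prespecified analysis, with an unfixed evaluation point. It is not a demonstrated loss of power. Under a raw-scale reading, power for a uniform d = 0.2 would be between about 12% and 63% for an assumed baseline mean/SD from 4 to 1 (15% to 69% under the favourable variant). Every one of these values is well below the planned 90%. Under a reading at the mean baseline, or in the ANCOVA without the interaction, the planned power is kept. The algebra is certain. The size depends on baseline values that the article does not supply and on a reading that it neither adopts nor excludes. Because the safe reading costs nothing to prescribe, it should be fixed in writing before the analysis.

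**What to change.** Adopt one prespecified rule for arm-by-baseline and apply it to both the mixed model and the ANCOVA. Either of the following works:

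1. Keep the interaction in both models, centre baseline at its overall mean across arms, and define the primary effect as the arm difference at T2 at the mean baseline, taken as an explicit contrast because arm by phase is also in the model.
2. Keep baseline as a main-effect covariate only in both models, define the primary effect as the T2 arm difference, and move arm-by-baseline to the exploratory moderation analyses already planned, preferably with baseline centred there too.

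Under either option, delete the rule that adds the interaction to the ANCOVA when the slopes check fails, so that the quantity estimated does not depend on a preliminary look at the data. If an analysis plan already states the centring and the contrast, it is enough to align the ANCOVA rule with it.

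The cost is analysis wording only. Sample size, data collection and schedule do not change, and moderation by baseline can still be estimated.
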